	Gut microbiome		**✓**		**✓**	**✓**
	Faecal metabolome		**✓**		**✓**	**✓**
Safety measures	Adverse events (AEs)			**✓**	**✓**	**✓**
	Serious adverse events (SAEs)			**✓**	**✓**	**✓**
Verification of compliance with the intervention					**✓**	
Special situations related to defecation (e.g., concomitant medications)			**✓**	**✓**	**✓**	**✓**

Note: The outcome measures, weekly mean frequency of defecation, weekly mean stool appearance score and weekly mean stool urgency score are calculated from the defecation diary. The defecation diary completed from day −14 to −1 will be used for volunteer selection and baseline data. The detection of gut microbiome will be conducted within 2 months after the end of follow-ups, and the detection of faecal metabolome will be implemented within 2 months when data analysis finds that the probiotics present significant effect on gut microbiome.

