
### Safety evaluation

2.10

Existed evidence shows that probiotics is safe, without significant adverse event (AE) compared with placebo group. Nevertheless, in the present study, four kinds of symptoms possibly related to probiotics are listed as possible AEs in the study, including symptoms may result from systemic infections, deleterious metabolic activities, excessive immune stimulation, and gastrointestinal side effects [39]. And severe AEs are those AEs result in volunteer's withdrawal, like hospitalization, disability, mortal danger, or death. When an AE occurs, the symptoms, time of onset, duration, causal relationship with interventions, and measures taken, will be accurately recorded during the study. Any serious AE will be recorded according to the corresponding criteria and emergency measures and promptly reported to the medical ethics committee of the first affiliated hospital of Nanchang university within 24 h, in addition, a separate AE report will be prepared. Judged from the AEs observed in the study, the safety of *L. plantarum* P9 powder will be evaluated as the following four levels: excellent (safe with no AE); good (relatively safe with moderate AEs that disappear on their own without any specific treatment); conditional (AEs that resolve after adopting certain measures and do not lead to study withdrawal); and unsafe (AEs that result in volunteer's withdrawal) [40].

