### Compliance monitoring and withdrawn

2.12

The L. *plantarum* P9 and placebo powder are supplied as treatment packs and packaged in boxes. At the beginning of administration phase, the probiotics or placebo packaging boxes enough for 28-day intervention are distributed to corresponding volunteers. Volunteers are required to keep all the used (empty) and unused treatment packs which are collected to check whether a volunteer takes the probiotics or placebo as the study's schedule. Based on the number of empty packs, the compliance rate is calculated for individual volunteer. A compliance rate ≥80% indicates a good compliance. To improve compliance, a WeChat group is established for the cohort of volunteers, and the study personnel can post messages via the WeChat group, reminding volunteers to take the samples as scheduled and complete the defecation diary (Appendix 2). In addition, each volunteer can receive 300 RMB as a reward once they complete the follow-up.

Volunteers can withdraw from the trial for the following reasons [1]: Persistent adverse reactions (cannot be resolved after taking certain measures) possibly involving the four kinds of AEs listed in “Safety evaluation part” [2,39] Volunteers can autonomously withdraw from the study at any time for any reason.

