### Data collection and monitoring

2.14

An independent data management team (DMT) is formed to periodically assess the study quality and safety. Volunteers are required to complete the defecation diary (Appendix 2) daily online and the DASS-21 (Appendix 3) online as scheduled in Table 1, both of which are promptly downloaded and collected by the data analysts. The data of demographic profiles, defecation diary (Appendix 2) and DASS-21 (Appendix 3) completed online by volunteers can downloaded as excel spreadsheets for further analysis. For gut microbiome and metabolomics test, volunteers have to prepare stool samples as the instructions of test kit at home, at day 0 (observing period of pre-administrating), 28 (observing period of administrating) and 42 (observing period of pro-administrating), all of which are timely collected, separately stored and sent for detection at −80 °C in a special stool storage kit from Guangdong longsee company (www.longseemed.com). The data of gut microbiome and metabolomics detected from stool samples will detected by Key Laboratory of Dairy Biotechnology and Engineering, Ministry of Education.

All the data will be submitted to the DMT for managing and monitoring. The DMT will promptly check the data and urge the data collectors to resolve it when uncertainty about the data occurs. All records that contain names, ID Number, or other personal identifiers (e.g., informed consent forms), are stored separately from study records. The database will be password protected by the DMT. The team also has the authority to carry out an interim analysis or terminate the next-step study according to the following situations [1]: if the probiotics does not present effect on gut microbiome, then the study will not further conduct the detections of faecal metabolome [3]; if any severe adverse events related to probiotics occurs, DMT will suggest terminating the study.

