### Statistical analysis

2.15

The following four datasets will be used for the analysis [1]: the data of all volunteers who completed the follow-up and [2] the data of three subgroups divided according to compliance (≥80%, 60–80%, and <60%), which will be analysed to validate the robustness of the analysis results. The following analysis methods will be used to analyse each dataset.

First, to analyse the inter-group differences in each outcome measure, Z test (as the sample size is quite more than 10, using Z test instead of Wilcoxon signed-rank sum test) will be used for the outcome measures, including the diarrhoea severity score, weekly mean frequency of defecation, weekly mean stool appearance score, weekly mean stool urgency score, and emotional state score, at each observation point. In the analyses, the *P*-value indicating statistical significance will be set at 0.05. More detailed information about how to analyse and present inter-group differences is clearly provided in Table 2.

**Table 2 tbl2:** The format to analyse and present the inter-group differences between probiotic and placebo groups at each observation point.

Groups	P5	P25	Median	P75	P95	Z value	*P*
*L. plantarum* p9							
Placebo							

Note: The data applied here includes the diarrhoea severity score, weekly mean frequency of defecation, weekly mean stool appearance score, weekly mean stool urgency score, and emotional state score; P5, P25, P75, P95 means the 5th, 25th, 75th, 95th percentile, respectively; Z = |T-n1*(N+1)/2–0.5|/SQRT [n1*n2(N+1)/12], n1 refers to the smaller sample size between the two compared groups, while n2 refers to the sample size of the other group; N = n1+n2; T is calculated using method of Wilcoxon signed-rank sum test.

Then, to identify the intra-group changing trends with the consecutive phases, namely, pre-, during and post-probiotic administrating, the *Kruskal-Wallis* rank sum test will be used for multiple comparisons of the diarrhoea severity score, weekly mean frequency of defecation, weekly mean stool appearance score, weekly mean stool urgency score, and emotional state score for each group, i.e., probiotic group or placebo group. In the analyses, the *P*-value indicating statistical significance will be adjusted to be 0.05/[k(k-1)/2], where k is the number of sample groups in the comparison. More detailed information about how to analyse and present inter-group differences is clearly provided in Table 3.

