## Trial status

4

This study started recruiting patients on October 1, 2020. To date, 174 patients have been enrolled. The enrolment is expected to be completed by October 31, 2022, and all follow-ups are expected to be completed by December 31, 2022. The protocol is 2.0 version, and the date of edition was September 10, 2020.

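### Withdrawal alone decides the unsafe level and defines severe AEs, so an unresolved AE in a volunteer who stays has no safety level

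*Protocol article*

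**What the plan says.** Section 2.10 (Safety evaluation) rates the powder on four levels. Excellent means that no AE occurred. Good covers AEs of moderate degree that clear without treatment. The third level is "conditional (AEs that resolve after adopting certain measures and do not lead to study withdrawal", and the fourth is "unsafe (AEs that result in volunteer's withdrawal". The same section states that "severe AEs are those AEs result in volunteer's withdrawal, like hospitalization, disability, mortal danger, or death". For every AE it records symptoms, onset, duration, causality and measures taken. Serious AEs follow criteria of their own and go to the ethics committee within 24 hours.

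Section 2.12 (Compliance monitoring and withdrawn) lists the grounds on which a volunteer can leave. The first is "Persistent adverse reactions (cannot be resolved after taking certain measures"; the second is the volunteer's free choice at any time.

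Section 2.14 (Data collection and monitoring) states that "if any severe adverse events related to probiotics occurs, DMT will suggest terminating the study". In Table 1 the last AE assessment is on day 42.

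**The concern.** Leaving a trial is a decision, and it measures harm poorly. Some people leave over a trivial complaint, and others stay with a lasting one. If withdrawal is the only condition for the worst level, the same persistent reaction makes the powder unsafe in one volunteer and has no level in another.

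Two things are at stake. The first is the safety verdict on the powder, which the abstract names as an aim and which this scale is meant to deliver. The second is the termination advice, because it depends on the word severe and section 2.10 explains that word through withdrawal.

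**Working it through.** The plan gives no figure on this point to reproduce. The check applies the four definitions in section 2.10, word for word, to every combination of severity (mild, moderate, severe), course (clears by itself, resolves after measures, does not resolve) and status (stays, withdraws): 3 × 3 × 2 = 18. Severity here means ordinary clinical intensity.

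| Severity and course | Stays | Withdraws |
|---|---|---|
| Mild, clears by itself | none | unsafe |
| Mild, resolves after measures | conditional | unsafe |
| Mild, unresolved | none | unsafe |
| Moderate, clears by itself | good | good and unsafe |
| Moderate, resolves after measures | conditional | unsafe |
| Moderate, unresolved | none | unsafe |
| Severe, clears by itself | none | unsafe |
| Severe, resolves after measures | conditional | unsafe |
| Severe, unresolved | none | unsafe |

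One level: 4 (stays) + 8 (withdraws) = 12. Two levels: 1. No level: 5. Total: 12 + 1 + 5 = 18.

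**The unresolved AE.** In a volunteer who stays it is not excellent (an AE occurred), not good (it did not disappear), not conditional (it did not resolve) and not unsafe (nobody withdrew). This holds at all three severities. An AE still open on day 42 is a concrete case.

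**The self-resolving AE.** In a volunteer who stays, only a moderate one has a level, because good is limited to moderate AEs. A mild or a severe one has none.

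**Does section 2.12 close the gap?** Its verb is permissive: a volunteer with a reaction that cannot be resolved can leave and may also stay. The same section pays 300 RMB on completing follow-up, so staying is a plausible choice.

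**The termination advice.** Set section 2.14 beside the severe-AE sentence in 2.10 and take two cases.

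- A volunteer leaves over a minor reaction judged related. The AE resulted in withdrawal, so on the literal wording it is severe and the advice is triggered.
- A volunteer is admitted to hospital for a related AE and stays in the study. Admission is among the examples, but the sentence presents the examples as AEs that result in withdrawal. Whether the advice is triggered is unclear.

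**The case against.** The strongest reply has four parts.

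1. The scale rates the powder, not single volunteers. It is ordered, and the worst level reached naturally applies. This stands. It removes any weight from the one combination that fits both good and unsafe, and it means that a count of ungraded volunteers would describe something the plan does not grade. It does not help the five combinations with no level: if such an AE is the worst that occurs, the powder has no rating.

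2. Section 2.12 lists persistent reactions separately from free choice, so they may be meant as a ground on which a volunteer is taken out. That is a possible intention, but the wording does not require it.

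3. The examples of severe AEs point to seriousness, the event must be related to the probiotic, and the DMT only suggests termination. This is fair, and it is why the point about the termination advice is limited to the literal reading. A rule that can stop a trial should still not need a generous reading.

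4. No safety data are lost, and the level is a descriptive label with no test attached. This also stands. A reader might infer that harms go unrecorded or that serious events escape reporting. The article does not support that: every AE is documented, and serious AEs have their own row in Table 1 and a 24-hour report.

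A reader might also infer that withdrawal is the only grading criterion. It is not. Presence of an AE, moderate degree and the way it resolved separate the first three levels. Withdrawal alone decides unsafe, and it bounds conditional.

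**Conclusion.** The point holds as a fault in stated rules. Following section 2.10 as written, 5 of 18 combinations, all in volunteers who stay, have no safety level, and they include every unresolved AE. On the literal wording, the termination advice in section 2.14 depends partly on leaving rather than on harm.

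The count assumes that the definitions are applied word for word and that section 2.12 leaves withdrawal optional. It counts logical cases and is not a frequency. The article gives no AE rates, so how often such a case will occur cannot be derived. The consequence is limited to the safety rating and the termination advice. Nothing here bears on the efficacy comparison, and the trial's validity is not in question.

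**What to change.** Amend section 2.10 as follows.

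- **(a) Severe AEs.** Use one definition of severe or serious by outcome (hospital admission, disability, threat to life, death), whether or not the volunteer withdraws, and use it for the termination advice in section 2.14.
- **(b) Levels.** State that the worst level reached applies to the powder. Define unsafe as any AE judged possibly related that is serious, is unresolved at the end of its follow-up (at least day 42), or leads to stopping the powder or to withdrawal. Widen good to mild or moderate AEs that clear by themselves and lead to neither. With severe defined by outcome, mild or moderate means every AE that is not serious. Say also that the scale covers possibly related AEs only and list the others by arm; otherwise an unrelated open AE would again have no level.
- **(c) Reporting.** Give the number of volunteers at each level by arm.

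Under (a) and (b), each of the 18 combinations, if possibly related, has exactly one level. Every serious, unresolved or withdrawal case is unsafe. The remaining cases are good if the AE cleared by itself and conditional if it needed measures.

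The cost is a short amendment with ethics approval, best made before unblinding. The trial status section reports that "To date, 174 patients have been enrolled" of a planned 200, but the change is still useful: duration, causality and measures are already recorded for each AE, so all volunteers' AEs can be graded under the new rules. The downside is that unsafe may be reached more often, so it must be read against the placebo arm, which is the purpose of (c).

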### Additional assessment

2.11

Demographic profiles, special situations related to defecation during the study, including change of dietary habits (e.g., eating spicy or oily foods or drinking), taking antibiotics and any other reported situation are recorded and assessed as needed.

### Compliance monitoring and withdrawn

2.12

The L. *plantarum* P9 and placebo powder are supplied as treatment packs and packaged in boxes. At the beginning of administration phase, the probiotics or placebo packaging boxes enough for 28-day intervention are distributed to corresponding volunteers. Volunteers are required to keep all the used (empty) and unused treatment packs which are collected to check whether a volunteer takes the probiotics or placebo as the study's schedule. Based on the number of empty packs, the compliance rate is calculated for individual volunteer. A compliance rate ≥80% indicates a good compliance. To improve compliance, a WeChat group is established for the cohort of volunteers, and the study personnel can post messages via the WeChat group, reminding volunteers to take the samples as scheduled and complete the defecation diary (Appendix 2). In addition, each volunteer can receive 300 RMB as a reward once they complete the follow-up.

Volunteers can withdraw from the trial for the following reasons [1]: Persistent adverse reactions (cannot be resolved after taking certain measures) possibly involving the four kinds of AEs listed in “Safety evaluation part” [2,39] Volunteers can autonomously withdraw from the study at any time for any reason.

### Sample size

2.13

The trial obeys the principle of a superiority design. Combined pilot cases observation and experts’ opinion [35,36], it is estimated that the primary outcome, diarrhoea severity score on day 28, can differ by 3 points between the probiotics or placebo groups, with a standard deviation of 6.8. Given an *α* = 0.05 and a *β* = 0.20, the sample size is calculated to be at least 81 per group. After considering the drop-out rate (20% or lower), the sample size should be 97 or more per group. The final sample size is determined to be 100 per group with a total of 200 cases.

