### Inclusion criteria

2.2

Eligible volunteers should have diarrhoea onset for at least 6 months before enrolment, with loose or watery stool (looked like Bristol type 5, 6, or 7 (Appendix 1) [33]) at least 25% of the times of defecation within the past 3 months. The volunteers involved in this study will be patients with chronic diarrhoea aged 18–65 years. For patients aged from 18 (exclusive) to 50 (inclusive) years, the result of stool test (including occult blood) conducted during the screening period is normal or is abnormal but is judged by the investigators as clinically irrelevant. For patients aged from 50 (exclusive) to 65 (inclusive) years, the result of colonoscopy performed at a tertiary or higher-level hospital within the past 6 months is normal or is abnormal but must be judged by the investigators as clinically irrelevant. Of course, the volunteers should be willing to sign the informed consent form, and only the written informed consent form is provided can then the volunteer participates in the trials.

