### Primary outcome

2.8

The primary outcome is the diarrhoea severity score, which is set as to the gastrointestinal symptom rating scale (GSRS) [[33], [34], [35], [36]]. The outcome measure is equal to the sum of mean defecation frequency score per day, mean stool consistency score per time, and mean stool urgency score per time within the past 7 days (see Appendix 2). The diarrhoea severity score will be assessed on days 0 (baseline), 14, 28, and 42. A higher score indicates more severe diarrhoea, Table 1. The details of calculation are as follows.

A defecation diary developed with reference to the literatures [33,34,37] will be completed daily online by the volunteers (Appendix 2). Based on the diary, the mean defecation frequency score per day, mean stool consistency score per time, and mean stool urgency score per time will be obtained. The defecation frequency score is ranked as: 0-point, one to two a day; 1-point, three to four times a day; 2-point, five to six times a day; 3-point, seven times a day or more frequently. The mean defecation frequency score per day is equal to “total defecation frequency score within the past 7 days/7”. The stool appearance score refers to Bristol stool type (Appendix 1) and must be recorded for each defecation: types 4–7 correspond to 0–3 points, respectively. The mean stool consistency score per time is equal to “total stool consistency scores within the past 7 days/total times”. The stool urgency score must be also recorded for each defecation: 0-point, no urgency; 1-point, a little urgency; 2-point, sudden need to have a defecation that must be addressed immediately; or 3-point, incontinence resulting in uncontrolled defecation and may stain pants. The mean stool urgency score per time is equal to “total stool urgency score within the past 7 days/total times”.

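### The sample size rests on a standard deviation of 6.8, but the primary score as defined runs from 0 to 9 and cannot have a standard deviation above 4.5

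*Protocol article*

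**What the plan says.** Section 2.13 (Sample size) of the protocol article plans a superiority trial on "the primary outcome, diarrhoea severity score on day 28". It states that this score "can differ by 3 points between the probiotics or placebo groups, with a standard deviation of 6.8", and attributes the figures to pilot cases and expert opinion, with two references. "Given an *α* = 0.05 and a *β* = 0.20", it reports that "the sample size is calculated to be at least 81 per group". It then allows for drop-out ("After considering the drop-out rate (20% or lower), the sample size should be 97 or more per group") and settles on 100 per group.

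Section 2.8 (Primary outcome) defines the score. "The outcome measure is equal to the sum of mean defecation frequency score per day, mean stool consistency score per time", and mean urgency score per stool, all over the preceding 7 days. The scoring is:

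- **Frequency:** 0 to 3 points per day; the weekly total is divided by 7.
- **Consistency:** from the Bristol type of each stool, where "types 4–7 correspond to 0–3 points, respectively"; the total is divided by the number of stools.
- **Urgency:** 0 to 3 points per stool; the total is divided by the number of stools.

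**The concern.** The two sections describe the same variable at the same visit, but the SD in one cannot arise from the scoring in the other. An average of items that each run from 0 to 3 also runs from 0 to 3, so the sum of three such averages cannot leave the range 0 to 9. An SD of 6.8 is too large for that range as a matter of mathematics, whatever the patients are like.

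Section 2.13 is the article's only justification for enrolling 200 volunteers. If its SD does not belong to the primary endpoint, the 80% power claim does not either, and a reader cannot tell what difference the trial is able to detect.

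**Working it through.** **Inputs.** Difference 3, SD 6.8, α = 0.05, β = 0.20, 81 per group, 20% drop-out and 100 per group finally (all section 2.13); item scoring 0 to 3 (section 2.8). Section 2.13 does not say whether α is two-sided; the two-sided value reproduces the stated number, whereas a one-sided value gives 64.

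**Step 1: reproduce the stated figure.** For two means,

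n per group = 2(z₀.₉₇₅ + z₀.₈₀)² × SD² / difference²

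= 2 × (1.960 + 0.8416)² × 6.8² / 3² = 2 × 7.849 × 46.24 / 9 = 80.65, rounded up to 81.

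This matches, so the formula was applied correctly to the stated inputs.

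**Step 2: range of the score.** Three components, each from 0 to 3: minimum 0, maximum 3 + 3 + 3 = 9.

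**Step 3: largest possible SD.** A variable confined to the interval from a to b has SD at most (b − a)/2, reached when half the values sit at each end. Here that is 9/2 = 4.5. Computed as a sample SD it is 4.53 for 81 people and 4.52 for 100. The stated 6.8 is 6.8/4.5 = 1.51 times the ceiling. If the two group means are also 3 points apart, the largest common SD falls to about 4.24.

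**Step 4: what the planned size gives on the 0–9 score.** With 20% drop-out, 100 × 0.8 = 80 completers per group.

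- *Power for 3 points at the 4.5 ceiling:* the standardised difference is 3/4.5 = 0.667; with 80 per group a t-test has about 98.7% power. Any smaller SD gives more.
- *Difference detectable with 80% power:* 2.80 × SD × √(2/80) = 0.443 × SD.

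The article gives no usable SD on this scale, so the first three rows below are assumptions chosen to show the range; the last is the mathematical ceiling.

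| SD on the 0–9 score | Detectable difference, 80 per group |
|---|---|
| 1.5 (assumed) | 0.66 |
| 2.0 (assumed) | 0.89 |
| 2.5 (assumed) | 1.11 |
| 4.5 (ceiling) | 1.99 |

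**Step 5: readings that might admit 6.8.**

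- *Change from baseline.* The range becomes −9 to 9 and the ceiling 9, but section 2.13 names the score on day 28, not a change. Even with the maximum SD of 4.5 at both visits and no correlation between them, the SD of the change is √(4.5² + 4.5²) = 6.36. Reaching 6.8 would need a negative correlation between baseline and day 28.
- *Negative points for Bristol types 1 to 3.* Section 2.8 gives these types no score. If they were scored −3 to −1, the range would be −3 to 9 and the ceiling 12/2 = 6.0, still below 6.8.
- *Raw weekly frequency in the sum.* The Discussion loosely says that the score is calculated from the weekly mean frequency, but it refers back to the primary outcome section, which uses the 0–3 frequency score.

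**The case against.** The strongest defence is that the error does no harm in the direction that usually matters. An SD that is too large leads to too many volunteers for a given difference, not too few; any feasible SD leaves ample power for 3 points; the remedy adds no patients; and 174 were already enrolled when the article was written. All of that stands. It limits the consequence but does not make section 2.13 correct.

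Four stronger readings are tempting, and the document does not support them.

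- **That the trial is underpowered.** It is not, for the stated 3 points. Whether it is adequate for a smaller difference depends on an SD the article does not give.
- **That the entry rule makes 3 points unattainable.** Section 2.2 requires loose stools in "at least 25% of the times of defecation within the past 3 months", so some volunteers could enter with low scores. But a 3-point difference between group means does not require each volunteer to improve by 3, and a 3-month eligibility proportion does not fix a 7-day score.
- **That results will be judged against 3 points.** Section 2.15 judges them by P < 0.05. Nothing in the article uses 3 points as a threshold for success or clinical relevance.
- **That 3 and 6.8 were borrowed from another instrument.** Section 2.8 links the score to the GSRS and shares references with section 2.13, so one may suspect it. The article does not say so, and the cited sources are not at hand.

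**Conclusion.** The point holds. The SD of 6.8 is about 51% above the largest value that the score in section 2.8 can have, and 81 per group at 80% power follows only from that value. The fault lies in the input, not in the calculation. The impossibility needs only the 0–3 scoring as printed and the statement that the sizing is on the day-28 score; it needs no assumption about the patients.

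The consequence is an unsupported power statement, not a trial shown to be too small. A 3-point difference is a third of the whole scale, which makes it ambitious as a planning target, though not thereby baseless. The smallest difference the trial could reliably find is unknown: about 0.443 × SD with 80 completers per group. The figures of 0.66 to 1.11 points illustrate this for assumed SDs of 1.5 to 2.5 and are not estimates. They also rest on a comparison of means, whereas section 2.15 plans a rank-based test.

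**What to change.** Keep 200 volunteers and rewrite section 2.13 so that it agrees with section 2.8:

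1. State where 3 and 6.8 came from and on what scale they were measured. If that scale is not the 0–9 score, stop using them for power.
2. Take an SD on the 0–9 score from the pilot diaries, or from the blinded pooled diary data of volunteers already enrolled.
3. Restate the power, or the detectable day-28 difference, for 100 per group (80 completers at 20% drop-out).
4. Do not present the detectable difference as a threshold of clinical relevance. It reflects the sample size and the SD, not what matters to patients.

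The cost is one blinded SD calculation and a rewritten paragraph, with no extra volunteers and no unblinding. The downside is that the quoted target difference and the power statement will change from those published.

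### The sample size is derived for a comparison of means but the planned primary test is an unadjusted rank-sum Z test; at the planned maximum drop-out, under normality, power is about 77–78% rather than 80%

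*Protocol article*

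**What the plan says.** The Sample size section (2.13) describes a superiority trial and expects that the day-28 diarrhoea severity score "can differ by 3 points between the probiotics or placebo groups", "with a standard deviation of 6.8". "Given an *α* = 0.05 and a *β* = 0.20", it reports that "the sample size is calculated to be at least 81 per group". It continues: "After considering the drop-out rate (20% or lower), the sample size should be 97 or more per group". Enrolment is then fixed: "The final sample size is determined to be 100 per group with a total of 200 cases". Sidedness and the test behind the calculation are not named.

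The Statistical analysis section (2.15) gives one between-group test for the primary score at each observation point, a Z test, justified thus: "as the sample size is quite more than 10, using Z test instead of Wilcoxon signed-rank sum test". The note to Table 2 shows what this Z is: a rank sum T, minus its null expectation n1(N+1)/2, with a 0.5 continuity correction, divided by the square root of n1·n2(N+1)/12. That is the normal approximation to the two-sample rank-sum test, although the text calls it signed-rank. Results are laid out as medians and percentiles. The main dataset is volunteers who completed follow-up. The day-0 score is collected (Table 1) but does not enter the test.

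**The concern.** A difference in points and an SD are the inputs of a comparison of means. If the trial is sized that way and then analysed by ranks, the 80% describes a test that will not be run. For normal data the rank-sum test has about 95.5% of the efficiency of the means test, so it needs a few more completers for the same power. The margin from 97 to 100 per group does not obviously cover both that and the drop-out. At stake are an accurate power statement and a few points of power that the baseline measurement could supply at no cost in volunteers.

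**Working it through.** **Inputs.** From section 2.13: difference 3, SD 6.8, α 0.05, power 80%, drop-out at most 20%, 100 enrolled per group. From section 2.15: rank-sum Z on completers. Assumed: two-sided testing (a one-sided calculation gives 64, not 81) and, where stated, normal data.

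**The plan's figure.** n = 2(1.960 + 0.842)² × 6.8² / 3² = 80.65, so 81 per group. It reproduces exactly as a normal-approximation comparison of two means.

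**Drop-out.** 97 is 81 × 1.2 = 97.2. Dividing instead gives 81/0.8 = 101.25, so 102. With 100 enrolled and 20% lost, 80 remain.

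**Completers needed by the rank-sum test, normal data.**
- Efficiency 3/π = 0.955: 80.65/0.955 = 84.5, so 85.
- From the t-test size: 81.6/0.955 = 85.5, so 86.
- Noether's formula: p = Φ((3/6.8)/√2) = 0.6225, and n = (1.960 + 0.842)² / [6(0.6225 − 0.5)²] = 87.2, so 88.

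**Power, normal data.** For the rank test, power = Φ[(3/6.8)√(0.955n/2) − 1.960]; for the means test the factor 0.955 is dropped. At n = 80 the rank test gives Φ(2.727 − 1.960) = Φ(0.767) = 77.8%. The simulated column applies the protocol's own Z statistic (40,000 runs per case).

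| Completers per group | Means test | Rank-sum, formula | Rank-sum, simulated |
|---|---|---|---|
| 80 (20% loss) | 79.7% | 77.8% | 77.2% |
| 81 | 80.2% | 78.3% | 77.5% |
| 85 (15% loss) | 82.0% | 80.3% | 79.6% |
| 100 (no loss) | 87.7% | 86.2% | 85.7% |

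The change of test costs about 2 to 3 points. The step from 81 to 80 completers costs only about half a point and comes from the drop-out inflation, not from the test.

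**Other shapes, same difference and SD, 81 per group, rank-sum simulated.** Uniform 75.8%; least favourable shift shape 73.3%; logistic 82.5%; exponential 97.8%. The means test stays at about 79–80% in all of them.

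**What baseline adjustment could recover at 80 completers.** With baseline correlation r, n/2 in the power formula becomes n/[2(1 − r²)]. The documents give no r, so these values are assumptions:

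| r | ANCOVA | Same, with efficiency 0.955 (approximate rank ANCOVA) |
|---|---|---|
| 0.2 | 81.3% | 79.5% |
| 0.3 | 83.3% | 81.6% |
| 0.5 | 89.7% | 88.3% |

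Simulation with normal data (20,000 runs) gives slightly less: 82.2% and 80.7% at r = 0.3.

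**The SD.** Section 2.8 defines the score as the sum of three components, each 0 to 3, so it runs from 0 to 9. An SD on that range cannot exceed half the range, 4.5, so 6.8 is impossible. If the 3 points were kept with SD 4.5, n = 2(2.802)² × 4.5² / 3² = 35.3, so 36 per group, and 80 completers would give 98.8% power with the means test.

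**The case against.** The case against is substantial. The 81 contains no arithmetic error, and sizing on means and then testing by ranks is a common approximation. The 20% is a ceiling: up to about 15% loss the rank test still has about 80% power under normality, and with no loss about 86%. No distribution is stated, and a plan that reports percentiles does not suggest normal data; for skewed or heavy-tailed scores the rank test gains power. Finally, every figure here rests on an SD that the score cannot have. All of this stands.

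A reader might therefore infer either that the 80% is simply not delivered, or that there is nothing to report. The documents do not support the first: the shortfall needs near-normal or flatter data and drop-out close to the maximum, and even then is a few points. The second goes too far. The planned test is the only between-group test given for the primary score, the power was not derived for it, and the document states no distribution that would justify relying on a gain from ranks. The impossible SD is the larger problem and makes true power unknown under either test. It is a further reason to redo the calculation, and does not reconcile the two sections.

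It is also fair that ANCOVA is partly a matter of preference and that its gain cannot be stated without a baseline correlation. That calls for stating the correlation as an assumption.

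**Conclusion.** The point holds in a limited form. The sample size was derived for a comparison of means, and the planned primary test is an unadjusted rank-sum Z test on completers. With the stated difference and SD, two-sided testing and normal data, power is about 77–78% at the 80 per group left after the maximum drop-out, against the intended 80%; about 85–86 completers are needed. At about 15% drop-out or less the target is met, and for heavy-tailed or skewed scores it may be exceeded. These figures measure the cost of the mismatch on the protocol's own inputs. They do not estimate the trial's true power, because an SD of 6.8 cannot occur on the defined score. The matter is modest and worth correcting because correction is cheap.

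**What to change.** Before unblinding, name a baseline-adjusted comparison of the day-28 diarrhoea severity score as the primary test: ANCOVA, or rank ANCOVA if ranks are preferred, with the day-0 score as covariate. Then restate the power for that test at 80 completers per group. Give sidedness, the assumed distribution and the assumed baseline correlation, with a range for the correlation. If the rank-sum Z test is kept, restate the power for it at 80 completers and call it a two-sample rank-sum test. In either case, replace the SD of 6.8 by one that is possible on the 0–9 score of section 2.8, and check that the 3-point difference refers to the same scale.

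The cost is a revised paragraph and a change to the wording of the primary test. The day-0 score is already collected, and no volunteers are added.
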